#### Blinding and randomization

Blinding of the principal researcher will be achieved by using the “study mode” of the DC stimulator. The study mode activates active and sham stimulation with digital codes. To minimize biasing the outcomes, an independent researcher creates a list of participants using block randomization. A randomization sequence is produced through random permutations generated by a stochastic process program in R software version 3.3.4. The size of the blocks will be set to 3 with a ratio of 1:1 so that we need six blocks of the collection (1. ABC, 2. BAC, 3. BCA, 4. CBA, 5. CAB, 6. ACB). We will draw six numbers randomly and sequentially from this collection.

In the randomization list the preprogrammed digital codes of tDCS and the size of the cathode electrode will be assigned to each participant for each session and submitted to the principal researcher via a sealed envelope. The independent researcher provides the digital code and cathode electrode size for the principal researcher prior to each tDCS session. The DC stimulator display continues to indicate the impedance and the time in the same fashion for both active and sham tDCS. The principal investigator will be blinded to the participant and experimental condition during the processing and analysing of the gait data. However, in the case of an adverse event, where it is necessary for the principal researcher to know which stimulation the participant is receiving, the principal researcher will be unblinded. Data from the identifiers will be removed and replaced by codes. However, the data will be re-identifiable by using the code or linking the participant’s details to their allocation and to their different datasets. Reliability of blinding will also be assessed after each tDCS session by asking participants about the type of stimulation they believed they had received [58]. The principal investigator will also guess and record which stimulation type the participant had received.

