**Methods:**

This study will be conducted in a randomized, double-blind cross-over design. Eighteen participants diagnosed with Parkinson’s disease will receive anodal and sham tDCS (1 mA, 20 min, 10 × 4 cm^2^) over the premotor and primary motor cortices with the cathode over the cerebellum during treadmill walking. Three montages will be applied over three sessions and compared: anodal tDCS with a small active cathode (4 × 4 cm^2^); anodal tDCS with a large, functionally inert cathode (10 × 10 cm^2^); and sham tDCS. The primary outcome measure is gait speed, and secondary outcome measures include gait parameters (temporospatial, segmental, kinematic), the Timed Up and Go test and lower limb muscle activity patterns as measured by electromyography.

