The anode will be placed centrally over the motor strip to cover a region 10–20% anterior to Cz during treadmill walking in all three sessions. To manage the risk of falls, participants will wear a harness if required. The position and size of the anode proposed in this study have been used by Kaski et al. [30, 33, 38] in a series of studies with positive effects on gait speed [30, 33, 38]. The cathode (either 10 × 10 or 4 × 4 cm^2^) will be placed over the cerebellum, 2 cm below the inion on the median line, over the three sessions. The cathode placement in the two active tDCS sessions will be counterbalanced across the participants. Thus, one third of the participants will receive active tDCS with a large cathode first, and another one third of the participants will receive active tDCS with a small cathode electrode first; the final third of the participants will receive sham tDCS with either a small or large cathode electrode (50% each). Electrodes will be inserted in saline-soaked sponge pockets. A cap and a strap will be used to attach the electrodes over the target locations. The current will be ramped up to 1 mA over 10 s in the active stimulation conditions and held constant for 20 min before ramping down over 10 s at the end of the stimulation [18]. In the sham condition, the current will be ramped up and down, at the beginning and at the end of the 20-min tDCS session (i.e. no active stimulation is administered in between). During both stimulation conditions (active and sham) all participants are asked to walk on a level Nautilus treadmill, and they will be allowed to use the hand rails. The principal researcher will apply the tDCS electrodes and oversee all aspects of the experiment. The tDCS will be terminated immediately if the participants become uncomfortable with it. The severity of adverse effects will be assessed using a scale suggested by Brunoni et al. [58] after each tDCS session.

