### Sample size

In preparation for the development of the protocol, the required sample sizes were calculated using Power Analysis and G* Power version 3.0. based on the primary outcome of gait velocity (measured by a 10-m timed walk, Kaski et al. [30]) and considering previously published cut-points for clinically meaningful difference in gait speed in people with PD: 0.02, 0.06 and 0.1 for small, moderate and large changes respectively [60]. The effect size derived from their study reflects the difference between a-tDCS and sham tDCS combined with physical training on gait velocity. To detect the difference followed by Kaski and considering a significance level of 5%, statistical power at 80%, significance level of 0.05 and delta of 0.05 and allowing for 20% drop-out across the trial, the sample size was calculated to be 18 participants, which allows for a complete cross-over randomization. We will employ some strategies suggested in the study of Little et al. (2012) for limiting data missing during conducting the trial [61].

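### As stated, the randomisation rule does not fix a three-session order for all 18 participants, and sham cathode size is given for only a third of them

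*Protocol article*

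**What the plan says.** Blinding and randomization sets the rule: "The size of the blocks will be set to 3 with a ratio of 1:1 so that we need six blocks of the collection". The collection is "1. ABC, 2. BAC, 3. BCA, 4. CBA, 5. CAB, 6. ACB", which is every order of three letters. Then: "We will draw six numbers randomly and sequentially from this collection". Whether draws are with or without replacement is not stated. Nor is it stated whether a string is one person's session order or a block of three people. The same section says that the stimulator code and "the size of the cathode electrode will be assigned to each participant for each session".

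The abstract makes this a three-condition cross-over: "Three montages will be applied over three sessions and compared". The Intervention section gives the first-session split: "one third of the participants will receive active tDCS with a large cathode first, and another one third of the participants" start with the small cathode. It continues: "the final third of the participants will receive sham tDCS with either a small or large cathode electrode (50% each". It also says that every participant has two active sessions and one sham session.

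The Sample size section says only that "the sample size was calculated to be 18 participants, which allows for a complete cross-over randomization". The Statistical analysis section nests participants in sequence as a random effect. It names condition and time, but no visit term.

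**The concern.** The analysis needs a sequence for every participant, and the randomisation list needs a condition and cathode size for every participant at every session. The stated block size, ratio and number of draws do not by themselves produce that list. A reader cannot reconstruct the allocation or tell whether the six orders were used equally.

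Equal use of the orders is what separates condition from visit in a three-period cross-over. If some orders are over-used and the model has no visit term, a practice effect across visits can pass into the condition contrast. Sham cathode size raises a similar question, because two thirds of the sham sessions have no stated rule.

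**Working it through.** **Inputs from the article.** 18 participants; 3 conditions, one per session; block size 3; six strings (3! = 6); six draws; first-session split in thirds.

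**The article's own arithmetic.** 6 blocks × 3 = 18, and 18 / 6 = 3 per sequence. Both are consistent, so 18 does permit a balanced six-sequence design.

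**Reading 1: a string is one participant's session order.** Six draws give 6 orders, and 18 − 6 = 12 participants have none. If the rule is extended to 18 independent draws, the probability of exactly three per order is 18!/((3!)^6 × 6^18) = 0.14%. At least one order is missing with probability 21.5%.

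**Reading 2: a string is a block of three participants, one letter each.** Each string holds each letter once, so six blocks always give 6/6/6. This matches the first-session split in the Intervention section. Only the first condition is fixed, and each person still has two possible orders for the remaining sessions.

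**Reading 3: a string is one order shared by a trio.**
- Without replacement: each order is used once for three people, so three per sequence.
- With replacement: P(all six orders appear) = 6!/6^6 = 720/46,656 = 1.5%. Expected distinct orders = 6 × (1 − (5/6)^6) = 3.99. P(first conditions split in thirds) = [6!/(2!2!2!)]/3^6 = 90/729 = 12.3%.

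**Reading 4: a block of three participants completed by cyclic rotation** (ABC gives ABC, BCA, CAB). The six strings form two cyclic families of three.
- Without replacement: three per sequence.
- With replacement: balance needs three draws from each family, C(6,3)/2^6 = 20/64 = 31.25%.

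The article states neither the replacement rule nor the trio or rotation step that Readings 3 and 4 need.

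**Ratio.** A two-part 1:1 does not describe three conditions (1:1:1) or six sequences (1:1:1:1:1:1).

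**Sham cathode.** One third of 18 is 6, and 50% each gives 3 small and 3 large. All 18 have a sham session, so 18 − 6 = 12 sham sessions have no stated rule for cathode size.

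**Conditional effect on type I error.** This was simulated under Reading 3, with an assumed within-person SD of 0.045 m/s, assumed practice gains at visits 2 and 3, no true condition effect, and a nominal 5% two-sided test of one condition contrast. The article gives neither the SD nor the gains.

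| Assumed gains (m/s) | Draws | Visit in model | Outcome | Type I error |
|---|---|---|---|---|
| 0.01 / 0.02 | with replacement | no | level | 6% |
| 0.02 / 0.03 | with replacement | no | level | 7–8% |
| 0.03 / 0.05 | with replacement | no | level | 10–11% |
| 0.05 / 0.08 | with replacement | no | level | 16–17% |
| 0.05 / 0.08 | with replacement | yes | level | 5% |
| 0.05 / 0.08 | without replacement | no | level | 0.8–0.9% |
| 0.05 / 0.08 | with replacement | no | pre-to-post change | 5% |

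Ranges reflect repeated simulation runs.

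**The case against.** The strongest defence is that the text is loose rather than wrong. The method refers to random permutations, lists six strings and draws six numbers. That sits more naturally with drawing each string once than with replacement. Without replacement, either completion rule gives exactly three per sequence and the stated split in thirds. The ratio may be shorthand for equal allocation, and a journal article may leave the mechanics to a fuller document. Much of this stands. It does not remove the point, because the article chose to state block size, ratio, collection and number of draws, and those elements do not by themselves yield the list it describes.

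Five stronger readings are tempting but not supported:
- **That no version of the procedure can give a balanced design.** Readings 3 and 4 without replacement do.
- **That the Sample size section claims six sequences with three people each.** It says only that 18 allows a complete cross-over, which is true.
- **That the trial is really a parallel-group scheme.** Codes and cathode sizes are assigned per participant and per session, so later sessions are in the list. What is missing is how their order was derived.
- **That trios share an order and so make allocation predictable.** The article never says that consecutive participants share an order.
- **That type I error is 16%.** That needs draws with replacement, gains of 0.05 and 0.08 m/s (the smaller equals the planning delta of 0.05) and a comparison of levels. The planned time-by-condition interaction uses pre and post measures from the same visit, so a visit-level shift largely cancels.

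**Conclusion.** The point holds as an incompletely fixed and partly inconsistent randomisation rule. It has not been shown that the allocation was unbalanced. Followed literally, the rule gives either a full order for 6 of 18 people, or a first condition for 18 with the other two sessions unordered. Balance depends on steps that the article omits. The 1.5% and 12.3% figures are exact, but they apply only if strings are drawn with replacement (for the 12.3%, one string per trio).

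The inferential cost is conditional. Without a visit term, type I error for a level comparison runs from about 6% to 17% over the assumed gains if draws were with replacement. If sequences are balanced, the same omission makes the test too conservative (below 1% at the largest assumed gains). A visit term brings both cases to about 5%. The sham cathode gap, 12 of 18 sham sessions without a stated rule, rests on no assumption.

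**What to change.** - Replace the rule of blocks of 3, ratio 1:1, with randomisation of participants to the six sequences in three permuted blocks of six, each block holding every sequence once in random order. This gives three per sequence and 6/6/6 by first condition. State the ratio as equal across the six sequences.
- Reconcile the Intervention section with Blinding and randomization, so that the rule for sham cathode size covers all 18 participants.
- The article reports a start in 2017 and expected completion in November 2018, so most lists have probably been issued. For these, state how the list was actually made, including the replacement rule and how sessions 2 and 3 were ordered. Report the realised number of participants per sequence.
- Add visit (period) as a fixed effect in the mixed model, whichever reading was used.

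The cost is a rewritten paragraph, a few lines of list code for any allocation not yet issued, and two model degrees of freedom for visit. Allocations already made stay as they are.

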#### Modelling electric field intensity (EFI)

We modelled the EFI using a computational model generated by a MATLAB toolbox, COMETS2, to simulate the two montages. Figure 3 compares the estimated EFI generated by the large anode and either a small or large cathode [59]. This illustrates that cerebellar activation is reduced using the 10 cm × 10 cm cathode.

**Fig. 3 Fig3:**
[figure not shown]
Current modelling results of electric field intensity

### Sample size

In preparation for the development of the protocol, the required sample sizes were calculated using Power Analysis and G* Power version 3.0. based on the primary outcome of gait velocity (measured by a 10-m timed walk, Kaski et al. [30]) and considering previously published cut-points for clinically meaningful difference in gait speed in people with PD: 0.02, 0.06 and 0.1 for small, moderate and large changes respectively [60]. The effect size derived from their study reflects the difference between a-tDCS and sham tDCS combined with physical training on gait velocity. To detect the difference followed by Kaski and considering a significance level of 5%, statistical power at 80%, significance level of 0.05 and delta of 0.05 and allowing for 20% drop-out across the trial, the sample size was calculated to be 18 participants, which allows for a complete cross-over randomization. We will employ some strategies suggested in the study of Little et al. (2012) for limiting data missing during conducting the trial [61].

### Gait data processing

The effects of the intervention on gait will be evaluated using a total of 21 gait parameters as listed in Table 1 [3]. The raw 3D position of each marker in GCS will be processed with the Vicon Nexus software to perform basic data processing (e.g. filtering at range of cut-off frequency of 5 Hz, detection and selection of gait events) and extraction of gait characteristics (e.g. spatial and temporal) as well as linear and angular kinematic analyses (e.g. position and orientation of segments and the centre of mass). The first and last gait cycles will be discarded to avoid considering gait initiation and termination, leaving at least three complete gait cycles for each limb available for analysis.

The gait events, including heel-contact and toe-off, will be detected manually based on the vertical displacements of the calcaneus and second metatarsal head markers respectively. All spatiotemporal parameters will be calculated using conventional methods as described by Cole [3]. Maximum toe clearance will be defined as the highest vertical displacement of the toe relative to the ground during the swing phase [62].

Sagittal plane angular kinematics of the trunk, hip, knee and ankle joints will be assessed. Trunk angle is the angle between the vector joining the sacral and C7 markers and the vertical axis of the GCS. Hip angle is defined as the angle between the vector joining the hip and knee joints and the knee and ankle joints. Ankle angle is the angle between the vector joining the knee joint and the 2nd metatarsal joint, where zero degrees is the point at which the two vectors are in a vertical position [3]. To measure segmental control, the mediolateral and vertical displacement of the head and pelvis will be assessed. Arm swing excursion will be reported by displacement of the wrists in the sagittal and frontal planes. All data in each gait cycle will be time-rescaled from 0 to 100 to facilitate averaging of all trials and reporting of events as a percentage of gait cycle. The gait data of each participant will be processed with the Vicon Nexus software, and all participants’ gait data will be merged using a code written in MATLAB (R2017a; The Mathworks, Natick, MA, USA).

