Clinical/screening measures					
Cognitive function	Addenbrooke’s Cognitive Examination (ACE-R)		✓		
Disease severity	Unified Parkinson’s Disease Rating Scale (UPDRS) and Hoehn and Yahr scale		✓		
Visual function					
Visual acuity	Binocular visual acuity: Bailey-Lovie			✓	
Contrast sensitivity	Pelli-Robson contrast sensitivity chart			✓	
	Melbourne Edge Test			✓	
Touch sensitivity	Semmes-Weinstein monofilament test			✓	
Clinical balance and gait	Tinetti Gait and Balance Instrument				✓
Mobility	Timed Up and Go (TUG) test				✓
Gait characteristics					
Spatiotemporal parameters	Nexus 2.6; Vicon, Oxford, UK				
Gait speed (m/s)					✓
Cadence (step/min)					✓
Spatial parameters (cm)	Nexus 2.6; Vicon, Oxford, UK				
Stride length					✓
Step length					✓
Step width					✓
Maximum toe clearance					✓
Temporal parameters (s and % GC)	Nexus 2.6; Vicon, Oxford, UK				
Stride/stance/swing/single support/double support/GC time					✓
Segmental linear motion (cm)	Nexus 2.6; Vicon, Oxford, UK				
Centre of mass (COM) VT/ML					✓
Head displacement, VT/ML					✓
Pelvis displacement, VT/ML					✓
Arm swing excursion					✓
Joint kinematics (deg)	Nexus 2.6; Vicon, Oxford, UK				
Trunk flexion angle					✓
Hip flexion/extension range					✓
Knee flexion/extension range					✓
Ankle dorsiflexion/plantar flexion range					✓
Joint angles (hip, knee, ankle) of stance and swing leg at maximum toe clearance					✓
Muscles activity (per muscle)	ZeroWire, Aurion Srl, Milan, Italy				
EMG onset and offset time					✓
Duration of muscle activity					✓
Total burst activation (integral of rectified EMG)					✓
Time of peak muscle activation					✓
Questionnaires					
Balance confidence	Activities-specific Balance Confidence (ABC) Scale	✓			
Freezing of gait (FOG) and falls	PD gait and falls questionnaire (FOG section)	✓			
Physical activity	International Physical Activity Questionnaire (IPAQ)	✓			
Quality of life	The 39-item Parkinson’s Disease Questionnaire (PDQ-39)	✓			

*AP* anteroposterior, *EMG* electromyography, *GC* gait cycle, *ML* mediolateral, *VT* vertical

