##### Electromyography

Muscle activation will be recorded at 1 kHz using the surface EMG bilateral ZeroWire system (ZeroWire, Aurion Srl, Milan, Italy). Recordings will be taken from the right and left lower limb muscles involved in gait: tibialis anterior, soleus, lateral and medial head of gastrocnemius, rectus femoris, biceps femoris, semitendinosus and vastus lateralis. Prior to applying the surface electrodes on the belly of the muscles of interest, participants with excessive hair over the muscles of interest will be shaved, using single-use disposal safety razors. Then, the skin will be cleaned thoroughly with a cotton ball and alcohol. This reduces impedance at the electrode-skin interface and improves the clarity of the myoelectric signal. After the skin is prepared, two Ambu surface electrodes (size 8 × 22/30 × 22; electrode diameter 30 × 20; inter-electrode distance 25 mm) will be placed on the muscles of interest according to the European recommendations for surface electromyography, Surface EMG for the Non-Invasive Assessment of Muscles (SENIAM) [56]. Muscle palpation will also be done to ensure validity of electrodes placement due to the anatomical variations between individuals.

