### EMG data processing

All EMG data will be sampled at 1000 Hz and be filtered post-processing using a Butterworth fourth-order band pass filter (10–500 Hz). The EMG will be full wave rectified and normalized to the peak EMG recorded for each muscle. The EMG will then be aligned with the selected gait cycles and temporally normalized to 100% of the cycle. EMG will then be averaged across all gait cycles for the left and right sides. Such methods will reduce the subject-specific and situation-specific conditions that may result in signal variance. The activation profiles of each of the muscles will be assessed, including EMG onset and offset time; duration and timing of muscle activity; average time to peak muscle activation; and total burst activation (integral of rectified EMG).

The gait and EMG data processing will be conducted by the principal researcher, and all of the research team will have access to the final trial dataset.

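### Two processing rules for secondary outcomes fail as written: the hip angle is defined as the knee angle, and the EMG band-pass ends exactly at the Nyquist frequency

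*Protocol article*

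**What the plan says.** **Joint angles.** The Gait data processing section announces four angles: "Sagittal plane angular kinematics of the trunk, hip, knee and ankle joints will be assessed". It then defines three of them. The trunk is the sacrum-to-C7 vector against the vertical. For the hip, "Hip angle is defined as the angle between the vector joining the hip and knee joints and the knee and ankle joints". For the ankle, "Ankle angle is the angle between the vector joining the knee joint and the 2nd metatarsal joint", with zero set by the position of two vectors although only one has been named. No knee definition follows. Table 1 (Clinical baseline assessment) has separate rows for "Hip flexion/extension range" and "Knee flexion/extension range". It also has an ankle range, and hip, knee and ankle angles of the stance and swing leg at maximum toe clearance.

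**EMG.** The Electromyography section says "Muscle activation will be recorded at 1 kHz". The EMG data processing section agrees on the rate and adds the filter: "All EMG data will be sampled at 1000 Hz and be filtered post-processing using a Butterworth fourth-order band pass filter (10–500 Hz"). Table 1 lists four EMG rows per muscle, and the Electromyography section names eight muscles on each side.

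**Status.** Gait speed is primary. Other kinematics and muscle activation are secondary (Primary and secondary outcomes).

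**The concern.** Both rules are stated explicitly, so the question is not whether detail has been left to a fuller document. It is whether the stated rule produces the named quantity.

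An angle between thigh and shank describes flexion at the knee. A hip angle needs a reference above the hip, such as the pelvis, the trunk or the vertical, and the printed definition has none. If it were applied as printed, a result labelled hip would say nothing about the hip, and a reader could not tell how the knee was measured. Kinematic outcomes go into the pre/post paired t tests and the linear mixed model (Statistical analysis), so the label matters for what those tests are about.

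For EMG, a digital band-pass must end below half the sampling rate. A rule that ends exactly there cannot be run, so whoever processes the data has to choose another one.

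**Working it through.** The plan gives no figure to reproduce here. Two direct checks suffice.

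**1. What the printed hip definition returns.** In the sagittal plane, with the pelvis upright, let the thigh be inclined to the vertical by the hip flexion h. The shank is then inclined by h − k, where k is knee flexion. The angle between the two vectors is h − (h − k) = k, so h cancels. With numbers:

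| True hip (deg) | True knee (deg) | Printed hip angle (deg) |
|---|---|---|
| +30 | 5 | 5.0 |
| −10 | 5 | 5.0 |
| +30 | 60 | 60.0 |
| 0 | 60 | 60.0 |

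A 40-degree change at the hip (+30 to −10) leaves the result at 5.0. The outcomes directly affected are one range and two toe-clearance angles (stance and swing leg), three in all.

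**2. Whether the EMG filter exists.** The inputs are a sampling rate fs = 1000 Hz and band edges of 10 and 500 Hz. Nyquist = fs/2 = 1000/2 = 500 Hz. The normalised upper edge is 500/500 = 1.0, and a digital Butterworth design needs it strictly below 1. The standard design maps an edge f to tan(πf/fs); at 500 Hz this is tan(π/2), which is unbounded. A design attempt in standard software fails with the message that critical frequencies must lie below fs/2. It fails for both readings of fourth-order: a prototype of order 4, and a prototype of order 2 that gives a band-pass of total order 4.

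Moving the upper edge just inside the limit shows what the rule amounts to (gain, prototype order 4):

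| Filter | 5 Hz | 10 Hz | 20 Hz | 100 Hz | 450 Hz | 490 Hz |
|---|---|---|---|---|---|---|
| 10 to 499.9 Hz band-pass | 0.062 | 0.707 | 0.998 | 1.000 | 1.000 | 1.000 |
| 10 Hz high-pass | 0.062 | 0.707 | 0.998 | 1.000 | 1.000 | 1.000 |
| 10 to 450 Hz band-pass | 0.061 | 0.707 | 0.998 | 1.000 | 0.707 | 0.002 |

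The first two rows agree at every frequency checked, so the 500 Hz edge removes nothing. An edge at 450 Hz gives a filter that can be built.

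**The case against.** The best defence of the hip sentence is that it is a hip definition and a knee definition run together with words lost. The rest of the article supports that. Four joint angles are announced. The marker set includes the anterior and posterior superior iliac spines, and leg length and joint widths are entered into Vicon Nexus (Three-dimensional gait assessment). Nexus is said to carry out the angular kinematic analyses (Gait data processing). The data for a proper hip angle will therefore exist, and the software is likely to use them. This stands as an explanation and makes real harm unlikely. It does not settle the text, which prints its own definitions and never says that Nexus outputs replace them.

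For EMG, the defence is that the intended processing is clear enough, because any workable reading keeps the 10 Hz lower edge. This also stands. An analogue stage before digitisation could have a 500 Hz limit, but none is described, and the text places the filtering after sampling.

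Three stronger readings are tempting but unsupported:

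- A reader might infer that knee results would be reported twice under two labels. That needs a knee definition, and there is none.
- A reader might count every hip, knee and ankle outcome as wrongly defined. Only the hip is. The knee is undefined and the ankle sentence is incomplete, and an article may leave such detail to the full protocol or to the source it cites.
- A reader might infer that an EMG cut-off chosen late would bias the comparison. The Blinding and randomization section has the principal investigator blinded while gait data are processed and analysed, although it does not name EMG. One cut-off applied to all three conditions of a within-participant design has no evident route to favour one of them. The Statistical analysis section also names no EMG test.

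**Conclusion.** Both rules are wrong as written, and the point is minor. The printed hip definition yields the knee angle and affects three secondary outcomes if it is followed literally. The 10 to 500 Hz filter cannot be designed at 1000 Hz sampling. All four EMG measures pass through that step, but the nearest workable version is a 10 Hz high-pass, so the effect on the results is probably small. No EMG data were available to measure it.

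The conclusion on the hip assumes that the article's definition governs. If Nexus model outputs are used, the error is confined to the text. The conclusion on EMG assumes a digital filter applied to the 1000 Hz recordings, as the text implies. Gait speed, the sample size and the randomization do not depend on either rule.

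**What to change.** **Joint angles.** Define the hip angle as the pelvis (or trunk) segment against the hip-knee vector, the knee angle as hip-knee against knee-ankle, and the ankle angle as knee-ankle against ankle-second metatarsal. Alternatively, state that the Vicon Nexus model outputs for these joints are used and delete the printed definitions.

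**EMG.** State an upper cut-off strictly below 500 Hz, or state a 10 Hz high-pass if no upper limit is wanted. The 450 Hz used above is only an example of a value that works; the documents give no basis for a particular figure. Set the choice before unblinding and apply it to every condition alike.

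The cost is a few sentences in the protocol or analysis plan. No new data are needed, since stored marker and raw EMG recordings can be processed under the corrected rules.
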